### Study Population, Setting, and Recruitment

This study aims to enroll 3 types of participants for the RCT and implementation process analysis. The first is doulas, who will be trained to deliver either the LHMoms intervention or the attention control variation of standard doula care to RCT participants. The second is birthing individuals participating in the RCT. The third comprises hospital staff, including clinical providers and hospital administrators, for the implementation process analysis phase. Three hospitals in NYC that serve low-income communities will be included: the NYP Brooklyn Methodist Hospital in Brooklyn, New York; the NYP Allen Hospital in upper Manhattan, New York; and the NYC Health + Hospitals Queens Hospital in Queens, New York. These sites were chosen because they serve underresourced individuals, including high numbers of Black, Latinx, low-income, and immigrant individuals.

The selection of doulas occurred before finalization of the intervention manual, approximately 8 months before RCT participant recruitment began at our first hospital site. Doulas will be selected and trained at the other 2 sites, approximately 8 months before participant recruitment, to allow time for training and certification. There will be 8 doulas per site, with 4 being assigned to the intervention arm and 4 being assigned to the control arm, for a total of 24 doulas across all sites. Purposive sampling is used in selecting doulas, who will be recommended by our community groups based on their interests and skills.

The recruitment period for the RCT will be staggered across years 2 to 6 of this study.

There will be an 18-month recruitment period at each hospital site, and we aim to recruit 200 participants per site for a total of 600 participants. At each hospital location, a community-based recruiter will be on-site. Research staff prescreen the EHR for eligible subjects and then discuss potential recruits with onsite principal investigators and hospital staff. The care team first approaches potentially eligible patients, inquires about their interest in LHMoms*,* and informs research staff about their willingness to be contacted. Research staff then approach eligible individuals within 48 hours after their delivery and before their hospital discharge.

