### Randomization and Informed Consent

At each of the 3 hospital sites, 200 participants will be enrolled and randomized, 100 per arm. The blinded study statistician creates the randomization design to randomize doulas and participants on an equal (1-to-1) basis. This study’s statistician, recruiters at each hospital, and study principal investigators remain blinded to randomization until the participant’s completion of the last study assessment, which is 6 months post hospital discharge. The randomization of participants occurs after the recruiter has obtained informed consent and completed in-hospital enrollment, before hospital discharge. The research program coordinator in the Weill Cornell Medicine Obstetrics and Gynecology Department is unblinded and executes the randomization of all RCT participants.

Doulas in both the intervention arm and attention control arm are assigned to the participants randomized to the respective arm, with no crossover, using block randomization, also designed by the blinded study statistician and executed by the unblinded research program coordinator. RCT participants are made aware of the arm to which they are randomized. Doulas and RCT participants are not blinded throughout this study, as both parties are inevitably aware of the program in which they are participating due to preparatory doula training and from session content.

After enrollment, while still hospitalized, all participants are given a home BP monitor and are taught how to take their BP using the device. All participants are asked to record BP values in a logbook provided by this study.

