### Statistical Analysis: Analysis of the Dual Primary End Points

Preliminary statistical analysis examines baseline characteristics between study arms (LHMoms intervention vs attention control) to verify that the randomization generated comparable groups. Categorical variables are summarized as frequencies and proportions. Statistical significance is set at *P*<.05 and tested using chi-square or Fisher Exact tests for variables with low expected frequencies (eg, <5). Continuous variables are described as mean, SD, median, and IQR. Statistical significance is tested using a 2-tailed Student *t* test or Wilcoxon Rank Sum for variables with unequal variance or skewed distributions.

The primary outcome of PPDS is operationalized as the presence or absence of PPD symptoms as indexed by an EPDS score greater than or equal to 9 (EPDS >9) at 6 months post partum (Table 4). Linear mixed models, designed to account for the nonindependence of observations within the same person that is inherent to repeated measures designs, are used to estimate the mean EDPS score with 95% CIs and make group comparisons between the LHMoms intervention and attention control at baseline and 6 months post partum. This approach enables an intention-to-treat analysis whereby all participants randomized into the trial are included in the primary analysis regardless of the number of sessions completed due to the flexibility of linear mixed models to handle the presence of missing data. Baseline characteristics associated with PPDS in univariate regression models (eg, parity) or group imbalance detected at baseline are included in linear mixed models as relevant covariates.

**Table 4 table4:** Primary and secondary outcomes measured in REDCap^a^ surveys assess psychosocial status and other health behaviors, as well as health care use and patient satisfaction.

Primary or secondary	Name of outcome	Specific measure to be used
Primary	PPDS^b^	EPDS^c^≥9
Primary	Cardiovascular health	LE8^d^ (continuous measure)
Secondary	Anxiety	GAD-7^e^
Secondary	Posttraumatic stress disorder	PCL-5^f^
Secondary	Perceived stress	PSS-10^g^
Secondary	Sleep	PSQI^h^
Secondary	Resilience	BRS^i^
Secondary	Social support	Perceived Social Support Scale
Secondary	Health care use	Contact at 7 days; 6 weeks postpartum visit attendance
Secondary	Satisfaction with postpartum care	CSQ-8^j^
Secondary	Implementation process	Focus groups, surveys, and interviews

^a^REDCap: Research Electronic Data Capture.

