^b^PPDS: postpartum depressive symptom.

^c^EPDS: Edinburgh Postnatal Depression Scale.

^d^LE8: Life’s Essential 8.

^e^GAD-7: General Anxiety Disorder Assessment.

^f^PCL-5: Posttraumatic Stress Disorder Checklist for DSM-5 (Diagnostic and Statistical Manual of Mental Disorders [Fifth Edition]).

^g^PSS-10: Perceived Stress Scale.

^h^PSQI: Pittsburgh Sleep Quality Index.

^i^BRS: Brief Resilience Scale.

^j^CSQ-8: Client Satisfaction Questionnaire-8.

To determine changes in the second primary outcome of cardiovascular health, we similarly compare LE8 scores from baseline to 6 months with a linear mixed model approach as previously described. Following published guidelines, the LE8 metric is summed into a 1-100 score [17,45]. In addition to comparisons of mean scores at baseline and 6 months post partum, changes in group mean scores across this period are compared (ie, the interaction between treatment and time, eg, heart health score from baseline to 6 months post partum in the intervention vs attention control participants). Components of the LE8 score include diet, physical activity, tobacco use, sleep, weight, cholesterol, blood glucose, and BP—each of the 8 elements is scored separately, and a summary score is created. An 80 or higher on the LE8 metric is considered ideal, with 50-79 being intermediate, less than 50 meaning poor, with a range of 0 (poor) to 100 (ideal). Prior work shows a 10-point change is considered clinically meaningful [46].

For both primary end points, given the longitudinal nature of the intervention, dose is an important effect for exploration. Additionally, we model a site (ie, hospital) effect as a fixed main effect and explore a site by treatment interaction (eg, given the potential for personnel [ie, doula] differences across sites, there is potential for a site-level difference in treatment response).

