### Sample Size Determination for Primary End Points

The EPDS scores from baseline to 6 months are used to analyze PPDS in LHMoms and control arms. While we considered PPDS and LE8 as dual primary end points, we chose 1 outcome to base our sample size on, which was PPDSs as defined by an EPDS score >9. This score was specifically chosen because it is used as the screening cutoff to refer for clinical evaluation in our hospital system, as it represents the possible presence of depressive or anxiety symptoms. The rate of EPDS >9 ranges from about 30% to 40% depending on other characteristics of the clinics (we selected 33.5% as the lower tertile of this observed range for our nonintervention group in the power calculation). We project we will observe a reduction in the PPDS proportion from 33.5% in the control arm to 23% in the intervention arm. This yields a minimum detectable difference of 31.5% lower incidence of PPDS in the LHMoms intervention arm compared to the attention control arm at 6 months. Our minimum detectable difference is calculated with a sample size of approximately 450 individuals (225 per study arm), assuming a 1:1 randomization, a design effect of 1.5 to account for variance among sites and doulas, a power of .90, a 2-sided significance level of 0.05, and a 20%-25% attrition. Our recruitment projection is for a sample of 600, 300 per arm; however, we have conservatively built in a 25% attrition rate for the longitudinal study (thus powering from a 450 analytic sample), although in past studies we have achieved 80%-85% retention in studies with a longer 1-year observation period [47-50].

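### The sample size allows for doula clustering but the stated primary models leave it out, so standard errors are too small: type I error for PPDS is above 5%, and about 11% if the whole design effect of 1.5 is due to doulas

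*Protocol article*

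**What the plan says.** All references are to the protocol article.

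- **Doulas and arms.** Study Population, Setting, and Recruitment: "There will be 8 doulas per site, with 4 being assigned to the intervention arm and 4 being assigned to the control arm", which makes 24 over three sites. Randomization and Informed Consent: "Doulas in both the intervention arm and attention control arm are assigned to the participants randomized to the respective arm, with no crossover". The same section gives 100 participants per arm at each site.
- **Sample size.** Sample Size Determination for Primary End Points builds in "a design effect of 1.5 to account for variance among sites and doulas". The calculation is for one outcome, the PPDS proportion.
- **Analysis.** Statistical Analysis: Analysis of the Dual Primary End Points uses linear mixed models, described as "designed to account for the nonindependence of observations within the same person that is inherent to repeated measures designs". Baseline covariates are added where relevant, and LE8 is analysed in the same way. For both end points the section continues: "we model a site (ie, hospital) effect as a fixed main effect and explore a site by treatment interaction".
- **Doulas in the analysis text.** They appear only as the reason for exploring that interaction. No doula random effect and no cluster-robust variance is stated.

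**The concern.** Participants are nested in doulas, and doulas in arms. The intervention effect is therefore estimated by comparing the clients of 12 doulas with the clients of 12 others. If doulas differ in how well their clients do, that variation belongs in the error of the comparison.

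None of the stated terms puts it there. A person-level effect is independent between two participants who share a doula. A fixed site effect removes differences between hospitals, not differences among the four doulas per arm within a hospital. An exploratory interaction does not alter the standard error of the main comparison.

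The sample size section shows that the sponsor expects such variance. Leaving it out of the analysis gives intervals that are too narrow and p values that are too small. A chance difference between two sets of doulas could then be reported as an intervention effect.

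**Working it through.** **Inputs from the article**

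- Two-sided alpha 0.05; power 0.90; 33.5% versus 23%; 225 per arm analysed; design effect (DE) 1.5 (Sample Size Determination).
- 24 doulas, 12 per arm (Study Population, Setting, and Recruitment).
- 600 randomized and 450 analysed, so 600/24 = 25 or 450/24 = 18.75 participants per doula.

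**1. The plan's own sample size.** The usual two-proportion formula with these inputs needs 385 per arm before the design effect, and 385 × 1.5 = 577.5, so 578, with it. The stated 225 per arm is not reproduced either way. Power at 225 per arm is 69.8% without a design effect. With it the effective size is 225/1.5 = 150 per arm and power is 52.4%. This is a separate problem, and the point here does not depend on it. It does mean that the sample size cannot show how the 1.5 was applied.

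**2. Which variance reaches the arm comparison.** With 100 per arm at each site and site as a fixed effect, a site's own level cancels from the difference between arms. Any real inflation must come from doulas or from site-by-treatment variation.

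**3. Size of the doula ICC implied by 1.5.** From DE = 1 + (m − 1) × ICC:

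- m = 18.75: ICC = 0.5/17.75 = 0.028
- m = 25: ICC = 0.5/24 = 0.021

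**4. Type I error when the inflation is ignored.** A test whose variance should be multiplied by DE, but is not, rejects under the null with probability 2 × [1 − Φ(1.960/√DE)]. Its standard error is 1/√DE of the correct one.

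| Doula DE | 1.960/√DE | Type I error | SE ratio |
|---|---|---|---|
| 1.0 | 1.960 | 5.0% | 1.00 |
| 1.1 | 1.869 | 6.2% | 0.95 |
| 1.2 | 1.789 | 7.4% | 0.91 |
| 1.3 | 1.719 | 8.6% | 0.88 |
| 1.4 | 1.656 | 9.8% | 0.85 |
| 1.5 | 1.600 | 11.0% | 0.82 |

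**5. Check by simulation.** The design was 24 doulas nested in arm, three sites as a fixed effect, a continuous outcome at one time point, and 20,000 runs per setting.

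| Per doula | ICC | Doula ignored | Doula-level t test, 20 df |
|---|---|---|---|
| 19 | 0.010 | 7.1% | 5.1% |
| 19 | 0.028 | 11.1% | 4.9% |
| 25 | 0.021 | 10.8% | 5.1% |

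A beta-binomial version with a 33.5% event rate and 19 per doula gave 11.2% at ICC 0.028. The 20 degrees of freedom are 24 doulas − 3 sites − 1 for arm.

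**6. Where the doula effect must enter.** Baseline is measured in hospital before discharge (Data Collection), ahead of any doula sessions. The analysis section also compares change between arms through the treatment-by-time interaction. A doula intercept that is the same at baseline and 6 months cancels from that contrast and would correct nothing there. The doula term has to act on the 6-month outcome.

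**The case against.** The strongest reply is that 11% is not established. A reader might infer that the type I error of this trial is 11%, but the documents do not support that. The 1.5 covers sites and doulas jointly, with no ICC and no split. If part of it was meant for sites, the doula share is smaller and so is the error. Doulas are themselves randomized, certified on every session, supervised weekly and, in the intervention arm, rated for fidelity. A low ICC is therefore plausible. This stands, and it is why the result is a range. It does not bring the error back to 5% unless doulas do not differ at all.

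A reader might also carry the 11% over to LE8. The article sizes the trial on PPDS alone and gives no design effect for LE8, so only the mechanism carries over.

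Neither simulation used the planned model with baseline and 6-month observations. Inflation in that model could be larger or smaller than shown. This stands as a limit on precision.

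Finally, the article condenses a fuller plan, and it does not rule out a doula term. A reader might infer that the sponsor rejected one; the text does not say so. But the article does more than stay silent. It states which correlation the models handle and which site term they carry, and this does not match the variance that its own sample size section assumes.

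**Conclusion.** The point holds in conditional form. Followed as written, the analysis understates the standard error of the arm comparison for both primary end points, because doula variance enters that comparison and no stated term accounts for it.

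For PPDS, the type I error of a nominal 5% test lies above 5%. It is about 11%, with standard errors about 18% too small, if the whole 1.5 is due to doulas. It falls to about 6% at a doula design effect of 1.1. This assumes roughly equal caseloads and that the design effect set for the PPDS proportion also describes the test used. For LE8 the direction is the same, and the size cannot be derived from the document.

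**What to change.** In both primary analyses, add a random effect for the originally assigned doula that acts on the 6-month outcome. Two forms would do this: a doula-by-time random effect in the repeated-measures model, or a doula random intercept in a 6-month model adjusted for baseline. Use a small-sample method such as Kenward-Roger or Satterthwaite, with about 20 degrees of freedom.

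Alternatively, use bias-corrected cluster-robust standard errors by doula. Any analysis of PPDS as a binary outcome needs the same protection. Keep the original assignment when a doula is replaced, since the article foresees replacements.

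The cost is one model term and a degrees-of-freedom rule. Doula assignment is run centrally by the unblinded coordinator, and analysis begins only in September 2029, so the change can be fully prespecified. Intervals become wider: by a factor of √1.5 = 1.22 if the whole 1.5 is due to doulas, plus a little for the t quantile. That is consistent with the design effect already assumed.

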### Sample Size Determination for Primary End Points

The EPDS scores from baseline to 6 months are used to analyze PPDS in LHMoms and control arms. While we considered PPDS and LE8 as dual primary end points, we chose 1 outcome to base our sample size on, which was PPDSs as defined by an EPDS score >9. This score was specifically chosen because it is used as the screening cutoff to refer for clinical evaluation in our hospital system, as it represents the possible presence of depressive or anxiety symptoms. The rate of EPDS >9 ranges from about 30% to 40% depending on other characteristics of the clinics (we selected 33.5% as the lower tertile of this observed range for our nonintervention group in the power calculation). We project we will observe a reduction in the PPDS proportion from 33.5% in the control arm to 23% in the intervention arm. This yields a minimum detectable difference of 31.5% lower incidence of PPDS in the LHMoms intervention arm compared to the attention control arm at 6 months. Our minimum detectable difference is calculated with a sample size of approximately 450 individuals (225 per study arm), assuming a 1:1 randomization, a design effect of 1.5 to account for variance among sites and doulas, a power of .90, a 2-sided significance level of 0.05, and a 20%-25% attrition. Our recruitment projection is for a sample of 600, 300 per arm; however, we have conservatively built in a 25% attrition rate for the longitudinal study (thus powering from a 450 analytic sample), although in past studies we have achieved 80%-85% retention in studies with a longer 1-year observation period [47-50].

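### Two primary end points, sized with the full two-sided 0.05 on one of them and no rule linking them: error is up to 9.75% if either may carry a claim, and the 0.90 is not the power for trial success if both must

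*Protocol article*

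**What the plan says.** Table 4 of the protocol article lists PPDS and LE8 both as primary, and the heading of the statistical analysis section calls them dual primary end points. The section Sample Size Determination for Primary End Points then says: "While we considered PPDS and LE8 as dual primary end points, we chose 1 outcome to base our sample size on". That one outcome is PPDS. Its calculation assumes "a reduction in the PPDS proportion from 33.5% in the control arm to 23% in the intervention arm". The analysed sample is 450, split equally between the arms, and clustering by site and doula is allowed for with a factor of 1.5. The error rates and dropout are set as follows: "a power of .90, a 2-sided significance level of 0.05, and a 20%-25% attrition".

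For LE8, the analysis section says: "To determine changes in the second primary outcome of cardiovascular health, we similarly compare LE8 scores". It refers back to the linear mixed model already described for the depression score, with estimates given as 95% confidence intervals. No SD, power or separate significance level is given for LE8.

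The article contains no division of alpha, no order of testing and no definition of trial success. The Discussion lists the two hypotheses joined by a plain 'and': at least 31.5% lower incidence of PPDS, and at least 1 point more improvement in LE8.

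**The concern.** With two primary end points, the significance level and power of the trial depend on the rule that links them. The three usual rules have different consequences:

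- **Either suffices.** Two tests at 0.05 give an overall error above 0.05 unless the level is adjusted.
- **Both required.** No adjustment is needed, but trial success is harder to reach than success on PPDS alone.
- **Fixed order.** The first end point keeps the full 0.05, and the second is tested only if the first succeeds.

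The article states none of these. It does commit the full 0.05 to one of the two primaries and takes its sample size from that. At stake is the case where the end points disagree. If PPDS misses and LE8 gives P<.05, the article does not say whether the trial has shown its primary effect. That case is realistic, because the article hypothesises an LE8 gain of at least 1 point but calls 10 points clinically meaningful, so the two end points may have very different power.

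**Working it through.** **Inputs from the article.** Two primary end points; two-sided alpha 0.05 and power 0.90, written for PPDS; PPDS 33.5% against 23%; 225 per arm analysed; design effect 1.5, so 225/1.5 = 150 effective per arm. The correlation between the two test statistics is not given. I take 0 to 0.7 as an assumed range.

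**1. Error if either end point suffices, each at 0.05, both null hypotheses true.**
Independent tests: 1 − (1 − 0.05)² = 1 − 0.9025 = 0.0975.
Correlated tests, from the bivariate normal as 1 − P(|Z₁| < 1.96 and |Z₂| < 1.96):

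| Correlation | Family-wise error |
|---|---|
| 0 | 0.0975 |
| 0.3 | 0.095 |
| 0.5 | 0.091 |
| 0.7 | 0.083 |

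The Bonferroni upper bound is 0.05 + 0.05 = 0.10. These figures count errors in both directions.

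**2. Power if both must succeed.** Joint power cannot exceed the smaller of the two single powers. Taking the stated 0.90 for PPDS at face value and assuming 0.90 for LE8 as well, independence gives 0.90 × 0.90 = 0.81, and correlation 0.5 gives 0.83. With LE8 power 0.80 and independence it is 0.90 × 0.80 = 0.72. These are illustrations only, because the article gives no SD for LE8. For SDs of 8 to 15 (my assumption), 225 per arm and no design effect, power for a 1-point difference runs from about 0.26 down to 0.11, while for 10 points it is about 1. Joint power could therefore be close to PPDS power or very low.

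**3. What Holm would cost PPDS.** When LE8 is not significant, PPDS must meet 0.025 instead of 0.05.
Power = Φ(0.105/SE − z), with SE = √[(0.335 × 0.665 + 0.23 × 0.77)/n], z = 1.960 at 0.05 and z = 2.241 at 0.025.

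| n per arm | SE | 0.105/SE | Power at 0.05 | Power at 0.025 | Loss |
|---|---|---|---|---|---|
| 225 (no design effect) | 0.0422 | 2.491 | Φ(0.531) = 0.70 | Φ(0.249) = 0.60 | about 10 points |
| 150 (design effect 1.5) | 0.0516 | 2.034 | Φ(0.074) = 0.53 | Φ(−0.208) = 0.42 | about 11 points |

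A pooled variance under the null changes these by less than one point (0.698 to 0.592, and 0.524 to 0.412).

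The plan's own 0.90 does not reproduce from these inputs. That is a separate finding, and the gap between 0.90 and 0.70 or 0.53 is not caused by multiplicity. If 0.90 at 0.05 is taken at face value, testing at 0.025 gives Φ(1.282 + 1.960 − 2.241) = Φ(1.000) = 0.84.

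**The case against.** The strongest reply is that this is an omission. Alpha allocation and the success rule are often left to the statistical analysis plan or full protocol, neither of which is shown, and either may already contain a rule. That stands in part: it cannot be said that no rule exists, or that one would be chosen after seeing results. It does not dispose of the point, because the article itself fixes the level and the sample size on one of two declared primaries. A later alpha split would not match the 0.05 used to size the trial, and a both-must-succeed rule would leave the 0.90 describing only part of what success requires.

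A reader might go further and infer that the trial, as written, has an error rate of nearly 10%. The article does not support that. It nowhere says that either end point is enough, and the hypotheses are joined by 'and', although that wording is not a decision rule either. The two-sided 0.05 is explicit only for the PPDS calculation; for LE8 it follows from the shared approach and the 95% intervals.

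A reader might also infer that the stated 0.05 and 0.90 are wrong whatever the rule. They are not. If both end points are required, 0.05 is correct. A fixed sequence with PPDS first would keep 0.05 for PPDS and control the overall error. The 0.90 is openly attached to the one outcome chosen for sizing and is never claimed for joint success.

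**Conclusion.** The point holds in conditional form. The article names two primary end points, uses the full two-sided 0.05 to size one, analyses the other the same way, and does not say how they combine.

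- If either may support a primary claim at 0.05, the family-wise error is up to 9.75% with independent tests, falling to 9.1% at correlation 0.5. This assumes that both null hypotheses are true and that LE8 is also tested at 0.05.
- If both are required, the error level is right, but the 0.90 is not the power for trial success, and that power cannot be computed from the article.
- If a fixed sequence with PPDS first is intended, neither problem arises, but the sequence has to be stated.

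This should be settled before the analysis, which is scheduled to begin in September 2029. It does not by itself invalidate the design.

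**What to change.** Pre-specify one rule that holds the overall two-sided level at 0.05, and state it in the protocol and the analysis plan:

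1. **Holm:** test the smaller p value against 0.025 and, if it succeeds, the other against 0.05. A claim on either end point is then protected. The cost is the 10 to 11 points of PPDS power shown above when LE8 is not significant. Restoring 0.90 for PPDS at 0.025 would take 455 per arm instead of 385, before any design effect or attrition.
2. **Fixed sequence:** test PPDS first at 0.05, and LE8 at 0.05 only if PPDS succeeds. PPDS loses no power, but LE8 cannot be claimed if PPDS fails.
3. **Both required:** each tested at 0.05. No alpha is lost, but one miss means the trial has not met its primary objective. An LE8 SD and target difference are then needed to state joint power.

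Under any of these, say that the 0.90 refers to PPDS alone and restate PPDS power at the level the chosen rule gives it. If an unseen document already contains a rule, it is enough to state that rule in the protocol and align the power text with it. The change needs only a short addition to the text and no new data.

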New York City (NYC) has increased community-based doula care to address the shortcomings of postpartum care for vulnerable communities. Doulas provide affordable nonmedical care during pregnancy, birth, and post partum. Doulas can extend physical, emotional, and informational support to people and their families [33]. They effectively increase satisfaction and lower the risk of severe maternal morbidity [34]. While doula care shows promise as a valuable resource for individuals in the postpartum period, most doula care in NYC is focused on intrapartum care, and evidence to support postpartum doula care is still evolving [35]. We propose to address these gaps by implementing and evaluating a doula-delivered intervention, Living Healthy for Moms (LHMoms), in 3 geographically distinct settings and populations (Brooklyn, Queens, and Northern Manhattan). We set out to culturally adapt an existing cognitive behavioral therapy (CBT) intervention delivered by nonspecialists for our NYC population, integrating cardiovascular health. We expected that doulas would be willing and able to receive training to deliver this intervention. The overall trial hypothesizes that participants completing the intervention will have lower prevalence of postpartum depressive symptoms (PPDS), better cardiovascular health, and greater engagement with postpartum health care than those receiving a variant of usual doula postpartum care [34,36].

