Participants in LHMoms are randomized to the intervention arm, where participants receive the doula-delivered CBT+cardiovascular health intervention, or the attention control arm, where participants receive a variation of standard doula-delivered postpartum care (based on a community-informed and provider-informed standardized checklist for doula care routinely used by one of our community partners, CWHA). Individuals are enrolled during delivery hospitalization and are consented and connected to their doulas in the hospital, predischarge. The intervention begins within the first week post hospital discharge and continues up to 6 months post hospital discharge. Throughout the 6 months, the intervention arm receives a total of 12 doula-led sessions. The attention control arm also receives a total of 12 doula-led sessions. Sessions for all participants are delivered via Zoom (Zoom Communications, Inc) or phone, based on the participants’ preference. All participants are fitted for and receive a home BP monitoring device and are trained on the correct way to use it before discharge. The LHMoms intervention arm begins with a 7-day emergency detection period, during which doulas contact participants daily within the first week at home to monitor MH and cardiovascular health, as the highest risk of severe maternal morbidity exists during this time period. The LHMoms study design is outlined below in Figure 1. The primary outcomes will be prevention of PPDS and cardiovascular health, measured at 6 months post partum. Doulas are supervised by this study’s psychiatrist or psychologist throughout this study, and all study data is entered into a REDCap (Research Electronic Data Capture) database maintained at the primary study site.

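### The 33.5% control rate is a background clinic rate applied, without justification or allowance, to a control arm that receives 12 doula-led sessions

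*Protocol article*

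**What the plan says.** All places are in the protocol article.

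- **Source of the rate** (Sample Size Determination for Primary End Points): "The rate of EPDS >9 ranges from about 30% to 40% depending on other characteristics of the clinics". From this range, "we selected 33.5% as the lower tertile of this observed range for our nonintervention group in the power calculation".
- **Use of the rate** (same section): the plan projects "a reduction in the PPDS proportion from 33.5% in the control arm to 23% in the intervention arm" and describes the result as a "minimum detectable difference of 31.5% lower incidence of PPDS in the LHMoms intervention arm compared to the attention control arm at 6 months". The other inputs are 225 analysed per arm, 1:1 allocation, design effect 1.5, power 0.90 and two-sided 0.05.
- **What the control arm receives** (Study Overview): "The attention control arm also receives a total of 12 doula-led sessions". The Attention Control Arm section spaces these sessions 1 to 2 weeks apart. Table 2 gives mostly infant-care topics, with some on the mother's own health and support.
- **Background care** (Shortfalls in Existing Postpartum Care): "most doula care in NYC is focused on intrapartum care, and evidence to support postpartum doula care is still evolving".
- **Hypothesis** (Discussion, Summary and Conclusions): a relative reduction of at least 31.5% against attention control participants at 6 months.

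**The concern.** The control rate in a sample size calculation should describe the arm that will be compared. Here the rate comes from clinics, is labelled as belonging to people without an intervention, and is then given unchanged to an arm with regular contact from trained and supervised doulas. An attention control is chosen because contact and support may themselves affect outcome. Giving that arm an untreated rate assumes that they do not, and the article never states the assumption. Nor does it say that the clinic rates come from people with postpartum doula care, or from 6 months after discharge.

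If the control sessions lower the proportion above the EPDS cutoff at all while LHMoms reaches its planned 23%, the tested difference is smaller than 10.5 points and power falls. A null result could then be read as LHMoms not working, although the trial would have measured only its increment over other doula support.

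**Working it through.** **Inputs** (Sample Size Determination for Primary End Points): control rate p1 = 0.335, LHMoms rate p2 = 0.23, 225 analysed per arm, design effect 1.5, two-sided 0.05, stated power 0.90. The effective number per arm is n = 225/1.5 = 150.

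**Formula** (two proportions, normal approximation, pooled variance under the null and unpooled under the alternative):

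power = Φ{ [ |p1 − p2|·√n − 1.96·√(2p̄(1 − p̄)) ] / √(p1(1 − p1) + p2(1 − p2)) }, with p̄ = (p1 + p2)/2.

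**Step 1: the plan's own figure.** p̄ = 0.2825, null SD term = 0.6367, alternative SD term = 0.6324.

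- With the design effect: (0.105 × √150 − 1.96 × 0.6367)/0.6324 = 0.060, so power is 52%.
- Without it: (0.105 × √225 − 1.96 × 0.6367)/0.6324 = 0.517, so power is 70%.

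Neither gives the stated 90%. For 90% power, 33.5% against 23% needs 385 per arm before the design effect, or about 578 with it. At 225 per arm the detectable difference at 90% power is 13.5 points without the design effect and 16.2 points with it, not 10.5. This arithmetic problem is separate from the source of the control rate, but any sensitivity analysis has to start from the corrected 52%.

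**Step 2: relative reduction.** 10.5/33.5 = 31.3%, against the stated 31.5%. The gap is rounding.

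**Step 3: vary the control rate.** The article gives no EPDS rate under attention-control doula care, so the lower rates are assumptions. The first two lower rates correspond to control sessions achieving 10% and 20% of the projected effect: 33.5 − 1.05 = 32.45 and 33.5 − 2.1 = 31.4. The third, 30%, is the low end of the clinic range and corresponds to one third of the effect (3.5/10.5).

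| Control | LHMoms | What is held | Relative reduction | Power, n = 150 |
|---|---|---|---|---|
| 33.5% | 23% | plan's inputs | 31.3% | 52% |
| 32.45% | 23% | LHMoms rate | 29% | 45% |
| 31.4% | 23% | LHMoms rate | 27% | 37% |
| 30% | 23% | LHMoms rate | 23% | 28% |
| 30% | 20.6% | relative reduction | 31.3% | 46.5% |
| 30% | 19.5% | 10.5-point difference | 35% | 56% |

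Without the design effect, 33.5% against 23% gives 70% and 30% against 23% gives 39%.

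**Step 4: direction.** Power falls if LHMoms stays at 23% or the relative reduction is held. It rises slightly, from 52% to 56%, if the absolute difference is held, but that requires LHMoms to reach 30 − 10.5 = 19.5%, better than the plan's own target.

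**The case against.** The strongest reply is that the article names the attention control arm in its detectable difference, so the sizing is for the comparison the trial makes, and that the label can be read as meaning only not LHMoms. On this view the plan assumes that control sessions do not move EPDS prevalence, which is a usual premise for an attention control. The text gives this some support:

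- Control doulas have no CBT or motivational interviewing training and avoid LHMoms topics (Doula Training and Creation of Intervention).
- They make no daily contact in the first week (Attention Control Arm).
- Their supervision involves no study psychologist (Doula Supervision and Assessment).
- The evidence for postpartum doula care is described as unsettled.
- LHMoms sessions also include doula care (Table 1, footnote d), so a shared support effect could lower both arms.
- The chosen value already sits in the lower part of the clinic range.

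Most of this stands. A reader might infer that the planned contrast and power do not apply to this trial at all. The document does not support that, because no passage shows a control effect on EPDS. A reader might also infer that every plausible scenario costs a material amount of power. The held-difference case shows otherwise.

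What does not stand is that the premise can go unstated. The article names a different kind of group as the source of the rate and gives no reason for carrying it over. The shared-effect argument preserves the 10.5 points only if LHMoms beats its own projected 23%.

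**Conclusion.** The point holds as a matter of unsupported input. A background clinic rate is used for a 12-session doula comparator, with neither a justification nor an allowance. With LHMoms at the planned 23%, the 10.5-point contrast is the most favourable case if the control sessions have any benefit. Power with the stated design effect would move from 52% to 45%, 37% or 28% at assumed control rates of 32.5%, 31.4% or 30%. At 30% it is 46.5% with the relative reduction held and 56% with the 10.5-point difference held.

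These figures rest on the normal approximation, 150 effective participants per arm, and control rates that have no source in the article for this arm. It would go too far to say that 30%, or anything below it, should become the base case. The shortfall from 90% to 52% at the plan's own rates is an arithmetic matter and does not come from the choice of comparator.

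**What to change.** 1. In Sample Size Determination for Primary End Points, describe 33.5% as a background clinic rate and state the assumption that the control sessions do not change it, with any supporting reason.
2. In the same section, restate power for 225 per arm with design effect 1.5 at 33.5% against 23% (52%) and the detectable difference at 90% power (16.2 points). Add the sensitivity rows from the table above, marked as assumptions and including the held-relative and held-difference cases.
3. In the Discussion (Summary and Conclusions), say that the 31.5% relative reduction assumes no effect of the control sessions. Add that a null result concerns the increment over doula-led attention control, not over postpartum care without a doula.

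The cost is some rewording, a short table and a less favourable stated power. This point calls for no added enrolment, visits or staff, and no particular lower control rate has to be adopted.
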